## Abstract

**Background:**

Uveitis, a group of disorders characterised by intraocular inflammation, causes 10–15% of total blindness in the developed world. The most sight-threatening uveitis affects the posterior segment of the eye (posterior-segment involving uveitis (PSIU)). Numerous different outcomes have been used in clinical trials evaluating alternative treatments for uveitis, limiting inter-trial comparison and aggregation of data. We aim to develop a core outcome set (COS) that would provide a standardised set of outcomes to be measured and reported in all effectiveness trials for PSIU.

**Methods:**

A three-phase design will be used informed by recommendations from the Core Outcome Measures in Effectiveness Trials (COMET) initiative. Phase 1: a comprehensive list of outcomes will be identified through both a systematic review of effectiveness trials of PSIU and qualitative research with stakeholders. The qualitative study will comprise focus groups with patients and their carers in parallel with one-to-one telephone interviews with health professionals and policy-makers. In the focus groups, patients will be grouped according to whether or not their uveitis is complicated by the sight-threatening condition uveitic macular oedema (UMO) since it is hypothesised that the presence of UMO may significantly impact on patient experience of PSIU. Phase 2: Delphi methodology will be used to reduce the range of potential outcomes for the core set. Up to three Delphi rounds will be used through an online survey. Participants will be asked to rate the importance of each outcome on a 9-point Likert scale where 9 is most important. Phase 3: a consensus meeting will be held with key stakeholders to discuss the Delphi results and ratify the final outcomes to be included in the COS.

**Discussion:**

The development of an agreed COS for PSIU would help ensure that outcomes which matter to key stakeholders are captured and reported in a consistent way. A COS for PSIU would allow greater comparison and aggregation of data across trials for the better evaluation of established and emerging therapies through evidence synthesis and meta-analysis to inform clinical guidelines and health policy.

**Trial registration:**

COMET. http://comet-initiative.org/studies/details/640. August 2015.

## Background

Uveitis describes a group of disorders characterised by intraocular inflammation responsible for 10–15% of total blindness in the developed world and up to 25% of blindness in the developing world [1–9]. Although uveitis may affect any age group, it peaks in the working-age population and has a disproportionately high impact in terms of years of potential vision loss [1] and need for long-term therapy with its socioeconomic impact being estimated to be at least as significant as that of diabetic retinopathy [9].

The most sight-threatening uveitis affects the more posterior structures of the eye, classified anatomically as intermediate, posterior and panuveitis [10, 11]. In clinical trials, these uveitic diseases are often grouped together as posterior segment-involving uveitis (PSIU) because of a number of shared features including their higher risk of sight-threatening complications and their requirement for systemic or local injection-based therapy. One of the most important complications in uveitis is uveitic macular oedema (UMO) which affects around one-third of patients with PSIU [1, 12–14]. UMO is a leading causes of sight loss in these patients and, due to its impact on the ‘central vision’ essential for reading, driving or recognising people’s faces, may be hypothesised to have a distinct impact on patients with PSIU.

There is currently a major unmet need in the treatment of PSIU with a paucity of high-level evidence to allow evaluation and licensing of therapies by regulatory authorities [15] and to inform treatment decisions by clinical experts and patients [16]. One of the major blocks identified in this area has been around ‘outcome measures’: the inadequacy of many of the standard outcomes used and inconsistency of the use of these outcomes between trials [15]. A systematic search of clinical trial registries noted that in 104 clinical trials of PSIU 14 different outcomes were used as a primary outcome, the most common being ‘visual acuity’ , ‘vitreous haze’ or ‘macular oedema’. Even where the same domain was used there was often variation in the way it was measured, analysed and reported [17]. This has seriously limited coherent evidence synthesis and meta-analysis in the field.

Inconsistent use and reporting of outcome measures can be addressed through the use of the core outcome set (COS). The COS is a standardised set of outcomes that have been scientifically agreed and are measured and reported in all trials for a specific clinical area [18]. The COS is not restrictive since other data can be collected, but rather ensures that certain key outcomes are always collected in a standardised way. This may profoundly enhance evidence synthesis by enabling comparison (due to the consistent collection of outcomes), reducing outcome-reporting bias (as the whole COS is reported) and improving the statistical power of any meta-analysis (more studies can be included). Development of the COS is supported by a number of initiatives such as the Core Outcome Measures in Effectiveness Trials (COMET) initiative [18] and has been endorsed by Cochrane and the World Health Organisation [19].

The development of a COS for PSIU would provide for the first time a standardised set of outcomes to be measured that has value to all stakeholders and can be used in all comparative efficacy or effectiveness trials in uveitis [20]. This has the potential to profoundly enhance evidence synthesis and reduce research waste [19, 21] with direct benefits to patients with sight-threatening uveitis.

### Aims and objectives

#### Aims

The aim of this study is to define a COS for PSIU for use in effectiveness trials in adult patients. In addition, we will evaluate any difference in priorities that arise from the presence or absence of the key sight-threatening complication, UMO.

#### Objectives

There are three specific objectives for the study:To identify a comprehensive list of potential outcomes based on (a) systematic review of clinical trials in PSIU and (b) findings from key respondent focus groups and interviews (patients, carers, health professionals, health policy-makers).To prioritise outcomes through a Delphi process, and to evaluate any potential impact of the presence or absence of UMO.To discuss the Delphi results and finalise the COS for PSIU through a consensus meeting with the key stakeholder groups (patients, carers, clinicians, policy-makers).

## Methods

A three-phase approach will be used to develop a comprehensive COS, in which any relevant outcome identified by any stakeholder will be considered. This may therefore include clinical parameters: patient-reported function, quality of life and health-economic factors, among others. First, a comprehensive list of outcomes will be identified through a review of outcomes reported in existing trials (systematic review) and qualitative research with stakeholders. Second, a Delphi process will be used, asking the stakeholders to prioritise outcomes for relevance through an online survey. Third, a consensus meeting will be held with key stakeholders to discuss the Delphi results and confirm the final outcomes to be included in the COS [22]. The study design is illustrated in Fig. 1.

**Fig. 1 Fig1:**
[figure not shown]
Flow diagram illustrating study design

### Phase 1: identifying a comprehensive list of potential outcomes to be included in the COS

#### Systematic reviews

A systematic review will be conducted on the effectiveness of pharmacological agents for PSIU (including PSIU with UMO) and potential outcomes will be identified for inclusion in the COS. The identified outcomes from the systematic review will be used to supplement the list of outcomes identified in the qualitative research. The combined list will be reviewed to make sure they provide clear meaning and no duplication [23].

Standard systematic review methodology will be employed to identify, select and extract data from comparative studies (randomised/non-randomised and observational studies) of pharmacological interventions in patients with UMO. Searches will be conducted through bibliographic databases (Cochrane Library, MEDLINE, EMBASE and CINAHL) and clinical trials registers. No restriction will be placed on either language or year of publication. Translation of non-English language articles will be undertaken to minimise selection bias. Data extraction will include the following: basic trial information and name, investigator names, year of study, primary outcome, secondary outcomes, method of measurement and analysis for all outcomes [23].

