Furthermore, since publication of the SUN criteria, a number of newer instrument-based measures have become available, notably optical coherence tomographic (OCT) measurement of macular thickness to detect and quantify macular oedema. Such measures provide objectivity and sensitivity to change that is attractive to researchers and triallists but may be less meaningful to patients. Our proposed COS methodology will address these issues by compiling a contemporary long list of potential outcomes derived from systematic review of trials in PSIU and additional outcomes identified by patients and other key stakeholders, which will then be prioritised through a Delphi approach and a consensus meeting to produce the final COS [37–41].

A potential influence on the output from the Delphi is the cut-off values for determining consensus. We have sought to reduce bias by stipulating these a priori. These cut-off values are estimated empirically with the purpose of avoiding two pit-falls: first that an outcome that is critical to one group might wrongly be excluded due to it being scored low by one or more other groups; and second that the criteria for consensus were too stringent for a significant number of outcomes, leading to excessive weight being placed on the consensus meeting where personal dynamics and stakeholder power may have disproportionate influence.

These issues also hint at the fundamental question of whether the views of all stakeholders are equal in the COS process, and if not, then how should this be weighted. One of the advantages of the COS is that it is not limited to a predetermined small number of outcomes – there is room for the most important outcomes from any and all key stakeholder groups, provided that consensus can be reached.

Identification of the core outcomes for inclusion in the COS is an important step, which will improve data synthesis and allow cross-study comparison. The next phase is to go on to identify and agree measures for consistent assessment of these core outcomes. Candidate measures for these outcomes will have been identified during this project. Future work will include the assessment of the suitability of specific measurement tools aligned to the COS based on their measurement properties including their construct validity, reliability and responsiveness.

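### The Systematic reviews section states two incompatible review populations, PSIU and UMO only, so the Delphi long list may not be comprehensive for PSIU

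*Protocol article*

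**What the plan says.** The Aims section sets the purpose of the study: "to define a COS for PSIU for use in effectiveness trials in adult patients". Three places outside the methods section describe the literature source in the same terms. The abstract has "a systematic review of effectiveness trials of PSIU and qualitative research with stakeholders", Objective 1 has "systematic review of clinical trials in PSIU", and the Discussion promises "a contemporary long list of potential outcomes derived from systematic review of trials in PSIU".

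The Systematic reviews section under Phase 1 opens consistently with this. Its subject is the "effectiveness of pharmacological agents for PSIU (including PSIU with UMO", so UMO is a subset of the review population. The second paragraph of the same section then turns to how studies will be found, chosen and abstracted. The studies it names are "comparative studies (randomised/non-randomised and observational studies) of pharmacological interventions in patients with UMO". Nothing else in the article defines which studies the review selects.

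The Background describes UMO as a complication "which affects around one-third of patients with PSIU", so the two populations are far from interchangeable.

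**The concern.** Two populations are given for one review, and the narrower one stands where the selection rule is stated. Someone screening a trial of PSIU without UMO would keep it under the first paragraph and reject it under the second.

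This matters because Phase 1 has only two sources for the long list, the review and the qualitative work, and its declared purpose is a comprehensive list. An outcome absent from the list cannot be rated in round one. If someone proposes it in the round-one free text, it is first rated in round two. If nobody proposes it, it receives no Delphi rating. What is at stake is therefore whether the list is complete for PSIU, the condition the core outcome set is meant to serve.

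**Working it through.** The article gives no figure to reproduce, so the check is a comparison of texts followed by the logic of what could be lost.

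**Step 1. Scope statements side by side.**

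| Place in the protocol article | Population |
|---|---|
| Abstract, Methods | PSIU |
| Aims (scope of the core outcome set) | PSIU in adults |
| Objectives, item 1 | PSIU |
| Systematic reviews, first paragraph | PSIU, UMO included |
| Systematic reviews, second paragraph (selection and extraction) | UMO |
| Discussion | PSIU |

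Four statements of the review's scope are PSIU-wide, as is the aim of the study. One is narrower, and it is the selection sentence.

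**Step 2. Apply both rules to three kinds of study.**

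- Study in PSIU with UMO: selected under both.
- Study in PSIU without UMO: selected under the first paragraph, not under the second.
- Study enrolling PSIU patients both with and without UMO: selected under the first paragraph. The second does not settle it, because it does not say whether all participants must have UMO.

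The second kind of study shows that the rules are incompatible. The third shows that the narrow sentence is also ambiguous in itself.

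**Step 3. What would be lost under the narrow rule.** Let W be the set of distinct outcomes extracted under the wide rule and N the set under the narrow rule. With UMO taken as a complication within PSIU, N is contained in W. An outcome is missing from the Delphi only if it lies in W but not in N and no other route supplies it. The other routes in the article are:

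- four initial focus groups, two of them in PSIU without UMO;
- about 15 to 20 interviews with professionals, policy-makers and commissioners;
- finalisation of the list with stakeholder representatives;
- the free-text question in round one.

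**Step 4. Can the loss be counted?** No. The article gives neither W nor N. The Background reports 14 different primary outcomes across 104 registered PSIU trials but does not split either figure by UMO status. The loss could be zero, if every outcome in W is also used in a selected study or raised by a stakeholder. The document gives no basis for an upper limit.

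**The case against.** The best reply is that this is a slip of the pen. Every other statement of scope is PSIU-wide, the intention is clear, and the article ranks neither sentence above the other. No search strategy or screening form is shown to prove that the narrow population was applied, and an article may properly leave those to a fuller review protocol. The review is also described as supplementing the qualitative work, and several other routes can bring outcomes in. The consensus meeting, too, may consider further outcomes where a clear rationale is given.

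Most of this stands. It is wrong to say that the review is restricted to UMO; what can be said is that the article contradicts itself. The other routes are real, and they limit the harm. The reply does not remove the contradiction, though. The population is not a detail left to another document: it is stated, in the methods, in a form that disagrees with the study's own aim. The section heading is plural, so the second paragraph might be meant as a separate UMO review, but the article does not say so, and the PSIU review would then have no selection sentence here.

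A reader might also infer that about two-thirds of the evidence is lost, from "uveitic macular oedema (UMO) which affects around one-third of patients with PSIU" and 1 − 1/3 = 2/3. That does not follow. The fraction counts patients, whereas a review selects studies and a long list counts distinct outcomes. The Background says that the PSIU subtypes are often grouped together in trials, so some trials may include patients with UMO and might qualify even under the narrow wording. No particular outcome is shown to be lost.

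**Conclusion.** The point holds as an internal contradiction in the review population. If the selection sentence is applied as written, outcomes used only in trials of PSIU without UMO are not extracted, and they reach the Delphi only if a stakeholder raises them. The long list may then fall short of comprehensive for PSIU. The size of the shortfall is unknown and may be nil. It depends on whether the narrow sentence was followed, on how trials with mixed populations were handled, and on how far outcomes overlap between UMO and other PSIU trials. The document settles none of these.

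A reader might go further and infer that the planned comparison of priorities with and without UMO is biased. The document does not support that. The comparison rests on the qualitative frameworks and on the Delphi scores, and both patient groups rate the same list item by item. An absent item cannot be compared, but no mechanism is shown by which scores on the listed items would be distorted.

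**What to change.** Rewrite the selection sentence in the second paragraph of the Systematic reviews section so that the studies are *in patients with PSIU (intermediate, posterior or panuveitis), with or without UMO*. This matches the first paragraph, the abstract, the Aims, Objective 1 and the Discussion. Check that the search terms and screening form use the same population. If a UMO-only search or screen has already been run, extend it before the long list is closed, so that any added outcomes can be rated from round one. Recording each study's UMO status and tabulating outcomes by it is optional; no stated objective needs it.

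The cost is one sentence. The only real burden is possible re-screening and extra extraction if work began on the narrow population. The article reports the study as ongoing at submission but does not say how far the review had progressed.

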#### Qualitative research

Potential outcomes to be included in the COS will be identified through focus groups with patients and carers, and one-to-one telephone interviews with health professionals, health policy-makers and commissioners.

#### Focus groups with patients and carers

##### Participants

Participants are patients with PSIU and their carers. To be included as a ‘Patient Participant’, the individual must: have a confirmed diagnosis of uveitis involving the posterior segment of the eye (intermediate uveitis, posterior uveitis or panuveitis) with or without macular oedema; have active follow-up for their PSIU; be at least 18 years of age; have the capacity to read and write the English language as well as good spoken English; and have the capacity to give written consent. Patient participants will be allocated to either the PSIU with UMO group or the PSIU without UMO group based on whether they have had UMO within the last 2 years. For inclusion as a ‘Carer Participant’, a carer is defined as a person at least 18 years of age (e.g. friend, family member or spouse) who provides unpaid and informal care to the patient during his/her illness and treatment journey for uveitis and UMO. Carers will attend the same focus group as the patient they are accompanying.

Patients will not be included if: they have purely anterior uveitis; or they have other unrelated ocular co-morbidities such as age-related macular degeneration, or diabetic retinopathy that might have significant impact on their vision and experience of uveitis. The presence of uveitis complications such as glaucoma, cataract, retinal vasculitis and choroidal neovascularisation are not exclusion criteria, but will be recorded and reported; these complications are not expected to segregate with either the UMO or non-UMO group and therefore should be approximately equally distributed. Nevertheless, if it was clinically felt that any of these complications was the main cause of vision impairment, those patients would be excluded. Peak central macular thickness will be reported for all patients in which OCT has been undertaken as part of their clinical care. Most recent best corrected visual acuity will be reported in all cases.

##### Recruitment

Patients will be recruited from the NHS Uveitis Clinics at the Birmingham and Midland Eye Centre (Sandwell and West Birmingham Hospitals NHS Trust) and University Hospitals Birmingham NHS Foundation Trust. Eligible participants (patients and their carers) meeting the inclusion criteria will be identified by ophthalmologists ([name] and [name]). A recruitment pack will be distributed and include an invitation letter and a participant information sheet. Written consent will be taken on the day of the focus group. The recruitment process and the consent pathway are illustrated in Fig. 1.

##### Sampling

To ensure a maximum range of views and opinions are collected [24], patients will be purposively sampled according to the following key characteristics: patients with uveitis with vs without UMO; patients with currently active vs inactive disease; age; and gender. We will aim to recruit approximately six participants per focus group, with a total number of participants for this stage anticipated to be between 24 and 30. Initially, four focus groups will be conducted, two each of PSIU with and without UMO, although further groups may be convened depending on judgements of data saturation [25].

#### Data collection (focus groups)

Focus groups will seek to identify outcomes that are important to patients and their carers. Whilst a variety of approaches will be utilised in order to understand participant perspectives, key areas for discussion will include the experience of uveitis and the impact on patients’ and carers’ lives; their hopes and expectations for treatment and life with uveitis; as well as discussion about outcomes that they would prioritise. A topic guide will be used to facilitate the focus group discussion. The focus group discussions will be audio-recorded.

#### One-to-one telephone interviews with health professionals, policy-makers and commissioners

##### Participants

Participants will include health professionals who are involved in caring for patients with PSIU, health policy-makers and commissioners with an influence on uveitis care. The use of telephone interviews facilitates wide geographical coverage and is felt to be more practicable for these participants [26, 27].

##### Recruitment

Recruitment of health professionals, health policy-makers and health commissioners will be via UK and international clinical, research and health service networks. Potential participants will be contacted via email containing an invitation letter and study information sheet, with a single reminder 2 weeks later. For those who agree to participate, a reminder will be sent 2 days prior to the interview date.

